### Intervention

The intervention involves a systematic and structured review of patients’ pharmacotherapeutic treatment plans to identify problems or risks associated with their medication regimens and propose changes or improvements. This procedure is part of the standard service portfolio of the regional healthcare authority and is conducted by pharmacists from the territorial Primary Care Pharmacy Unit. The intervention is based on the protocol outlined in the document “Rational use of medicines. Basic medication management in chronic patients: Reconciliation, review, desprescription, and adherence (Departament de Salut, 2013).

The review process includes two phases. In the first phase, individual pharmacological treatment plans are reviewed to identify DRPs, which are classified into four types: indication-related, appropriateness, effectiveness, and safety issues. Indication-related DRPs include medications. Without a current indication or missing necessary medications.

Appropriateness-related DRPs assess dosage, frequency, regimen, and duration, as well as the suitability of medications based on age, renal and hepatic function, and other clinical parameters. To identify potentially inappropriate medications by age group, we used the reference “Potentially inappropriate medications for the elderly” (Servei Català de la Salut, 2020), which integrates the Beers Criteria (American Geriatrics Society Beers Criteria Update Expert Panel, 2019), STOPP-START criteria (O'Mahony et al., 2015), Priscus List (Holt et al., 2010), and EU-PIM List (Fick et al., 2015), providing justification, recommendations for change and the criteria on which these recommendations are based. Effectiveness-related DRPs assess therapeutic outcomes in relation to clinical goals and identify instances of overtreatment or the need for de-intensification based on the patient’s health status.

Safety-related DRPs include therapeutic duplications, contraindications, adverse effects, allergies, drug interactions, or insufficient laboratory monitoring.

In the second phase, pharmacists issue proposals to optimize pharmacotherapy in response to identified DRPs. Recommendations may include discontinuation, substitution, therapeutic equivalents, initiation of new treatments, dosage or frequency adjustments, or enhanced monitoring.

These recommendations are then evaluated and agreed upon by a committee composed of the responsible physicians and the pharmacist. Consensus-based proposals are subsequently discussed with the patient or their legal representative, leading to a shared decision. Recommendations may be accepted or rejected.

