### Measurement

Data were collected at baseline and at 3 months using the electronic prescription module of each patient’s electronic health record. The evaluation was conducted by the pharmacist implementing the intervention, who was not blinded to the study group allocation of nursing homes and patients (Table 1).➢ Outcome variables

**TABLE 1 T1:** Variables and measuring instruments.

Variable	Instrument	Application time	
		Basal	3 months
Sociodemographic variables	Questionnaire *ad hoc*	X	
Age			
Sex			
Length of time living in the nursing home			
Pharmacotherapeutic plan			
Description of the pharmacotherapeutic plan	ATC classification^a^	X	
Description and classification of the DPRs^b^ detected	Classification	X	
Clinical			
Comorbidity			
*Physical comorbidity*	Checklist	X	
*Psychiatric comorbidity*	Checklist		
*Global indicator*	*Charlson index*	X	
Complex Chronic Patient^c^	Checklist	X	
Advanced Chronic Care Model^c^	Checklist	X	
Functional capacity	Barthel index	X	
Cognitive status	SPMSQ^d^ Pfeiffer		
Clinical Results			
Drug related problems (DRP)^b^	Questionnaire *ad hoc*	X	X
*Number of DR P* ^b^ *per patient*			
*Proportion of patients with DRP*			
Polymedication	Questionnaire *ad hoc*	X	X
*Number of drugs a patient receives simultaneously*			
*Number of polymedicated patients*			
Results of the pharmaceutical review (only in the intervention group)			
Proposals for change	Questionnaire *ad hoc*	X	
Proposals implemented	Questionnaire *ad hoc*		X

^a^
ATC: anatomical therapeutic chemical classification system.

^b^
DRP: drug related problems.

^c^
According to the criteria of *Bases per a un model català d’atenció a les persones amb necessitats complexes. Conceptualització i introducció als elements operatius. Generalitat de Catalunya, 2017.*

^d^
SPMSQ: short portable mental status questionnaire.

Drug-Related Problems (DRPs) were quantified as total number, DRPs per patient, and the proportion of patients with at least one DRP. DRPs were classified into four categories: indication, appropriateness, effectiveness, and safety (Table 2).

**TABLE 2 T2:** List and classification of drug-related problems (DRP) considered in this study.

Category	DRP
Indication	- Medically unnecessary/not indicated/not appropriate for the health problem - Failure to prescribe a necessary medicine
Adequacy	- Medically inappropriate - Dose higher or lower than correct dosage - Incorrect administration frequency - Wrong drug form - Duration too long or too short

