## Statistical methods

### Sample size

Based on prior observations and published studies, we assume that the proportion of patients with drug-related problems (DRPs) will be 50% in the control group (Vink et al., 2011; Costa et al., 2016; Garin et al., 2021). We expect to detect an absolute reduction of 10 percentage points in the prevalence of medication-related problems, from 50% in the control group to 40% in the intervention group. This difference is considered clinically meaningful, as even a modest reduction in such problems may lead to significant improvements in patient safety and care quality in the nursing home setting.

The sample size is calculated to account for the cluster design of the study, using the GRANMO calculator (https://www.datarus.eu/en/applications/granmo/). Assuming an alpha risk of 0.05 and a power of 0.80 in a two-sided test to detect a difference between proportions of 0.50 in the control group and 0.40 in the intervention group, a total of 24 clusters (12 per group) with 37 participants per cluster is required, including an estimated 10% loss to follow-up. A low intraclass correlation coefficient (ICC) of 0.001 is assumed. In the absence of published ICC estimates for this setting, we adopt a conservative value consistent with other studies involving individual-level binary outcomes with limited clustering. If the actual ICC or the number of participants per cluster differs substantially from expectations, we will conduct a sensitivity analysis to assess the potential impact on statistical power and precision.

Participants who die during the follow-up period will be considered lost to follow-up and excluded from outcome analyses. This expected attrition has been accounted for in the sample size calculation, which includes an estimated 10% loss due to mortality and other causes of dropout.

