According to a meta-analysis evaluating pharmacist-led interventions within multidisciplinary teams (physician, nurse, pharmacist) in nursing homes, such interventions led to a reduction of 2.2 DRPs (0.28–4.12; I^2^ = 44%, p = 0.02) based on the MAI criteria, a mean reduction of 1.9 medications, and an intervention acceptance rate of 69.8% (Lee et al., 2019).

The results of this study will inform the real-world utility and feasibility of the evaluated intervention and its implementation process, including the evolving role of the primary care pharmacist within a multidisciplinary team. This information will be valuable in refining the medication review program and optimizing its practical implementation.

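### The plan does not fix how a baseline DRP is scored at 3 months after its proposal is rejected, and the unblinded assessor took part in that decision in one arm only

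*Protocol article*

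**What the plan says.** **Process in the intervention arm (Methods, Intervention).** The pharmacist first identifies DRPs and then issues proposals. "These recommendations are then evaluated and agreed upon by a committee composed of the responsible physicians and the pharmacist". Agreed proposals go to the patient or legal representative for a shared decision, and "Recommendations may be accepted or rejected". Who may reject is not specified.

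**Process in the control arm (Usual care; Ethical aspects).** Treatment follows standard procedures. No review committee is described, and control residents receive the programme only after follow-up.

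**Outcome scoring (Measurement).** Data come from the electronic prescription module at baseline and 3 months. "The evaluation was conducted by the pharmacist implementing the intervention", and that pharmacist knew the allocation. Table 1 has DRP number and proportion recorded at both times on an ad hoc questionnaire. The description and classification of detected DRPs is marked at baseline only. Proposals made and proposals implemented are recorded in the intervention group only.

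**Acknowledged limitation (Discussion).** The article concedes that assessment is unblinded and made by the intervening pharmacists. It argues that the risk is reduced because outcome data are structured record variables that assessors cannot alter.

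**The concern.** A DRP is a finding about a prescription, and several Table 2 types call for opinion: whether a drug is needed, whether it is the most effective option, whether treatment should be less intensive. In intervention homes the assessor hears the physicians' and patient's reasons between the two scorings. In control homes nobody supplies such reasons. If a reason persuades the pharmacist that a baseline DRP was not a problem after all, it may not be scored again at 3 months, although the prescription is the same. An equally doubtful DRP in a control home stays counted.

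As tabulated, the 3-month DRP data are a count and a proportion, so a DRP explained away would look the same as one corrected. Number of DRPs per patient and proportion of patients with DRPs are both primary outcomes (Statistical method). At stake is whether a lower DRP count in the intervention arm can be read as better prescribing.

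**Working it through.** **1. The plan's own sample size reproduces.** Inputs from Sample size: "Assuming an alpha risk of 0.05 and a power of 0.80 in a two-sided test"; the proportion with DRPs falling "from 50% in the control group to 40% in the intervention group"; an ICC taken as 0.001; and, for the resulting size, "a total of 24 clusters (12 per group) with 37 participants per cluster is required, including an estimated 10% loss to follow-up".

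- Per arm, pooled variance: [1.960 × √(2 × 0.45 × 0.55) + 0.842 × √(0.25 + 0.24)]² / 0.10² = 388. Unpooled variance gives 385.
- Design effect: 1 + (37 − 1) × 0.001 = 1.036.
- With 10% loss: 388 × 1.036 / 0.90 = 447. Unpooled: 385 × 1.036 / 0.90 = 443.2, or 36.9 per home, which rounds up to 37.
- Stated: 12 × 37 = 444 per arm. This agrees, and the sample size is not in dispute here.
- Effective n per arm: 444 × 0.90 / 1.036 = 385.7, giving power 0.798 against the stated 0.80.

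**2. What re-scoring alone could do to the proportion with any DRP.** Assume a true 50% in both arms at 3 months, no treatment change, and a share s of DRP-positive intervention residents re-scored as DRP-free. Observed prevalence is 0.50 × (1 − s). The last column is the chance of a significant result favouring the intervention at effective n 385.7, so it rests on the plan's ICC.

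| s | Observed prevalence | Chance of significance |
|---|---|---|
| 5% | 47.5% | 0.10 |
| 10% | 45.0% | 0.28 |
| 15% | 42.5% | 0.55 |
| 20% | 40.0% | 0.80 |

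Re-scoring 20% of affected residents would imitate the whole planned difference. But a resident becomes DRP-free only if every DRP is dropped, so s depends on how many DRPs each resident has.

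**3. Linking s to rejected proposals (illustration).** The Discussion cites a meta-analysis with "an intervention acceptance rate of 69.8" per cent, so 1 − 0.698 = 0.302 are not accepted. Assume one proposal per DRP, every non-accepted DRP dropped, and k independent DRPs per affected resident. Then s = 0.302^k.

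| k | s | Observed prevalence | Chance of significance |
|---|---|---|---|
| 1 | 0.302 | 34.9% | 0.99 |
| 2 | 0.091 | 45.4% | 0.24 |
| 3 | 0.028 | 48.6% | 0.06 |

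This is the extreme case. If only one in three non-accepted DRPs were dropped, the per-DRP share is 0.302 / 3 = 0.101. With k = 2, prevalence is 0.50 × (1 − 0.101²) = 49.5%.

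**4. The same for DRPs per patient.** The mean falls by the per-DRP share whatever k is. Dropping all non-accepted DRPs lowers it by 30.2%; on the 2.2 to 4 DRPs per patient cited in the Introduction, that is 0.302 × 2.2 = 0.66 to 0.302 × 4 = 1.21. Dropping one in three lowers it by 10.1%, about the 10% reduction the Abstract expects. The one-in-three share is an assumption with no source in the article.

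**5. Medication counts.** Number of drugs and the threshold of ten or more follow counting rules set out under Measurement. A committee reason does not change them.

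**The case against.** Several counter-arguments have force.

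- A reader might infer that the committee rejects DRPs and that they vanish from the outcome by rule. The text does not support this. Recommendations are accepted or rejected, not DRPs, and the patient may be the one who declines. An unimplemented proposal could just as well leave the DRP counted. This stands, and the point is limited to a risk left open.
- Data come from the prescription record at both times, and proposals made and implemented are recorded, so rejected items could be compared with 3-month DRPs. This holds in part. The source is the record, but the DRP is a reading of it, and the proposal fields exist in one arm and are not linked to the outcome score.
- The Discussion already concedes unblinded, non-independent assessment. That covers the general bias. Its mitigation argument does not cover this route: the prescription can stay exactly as it was while the judgement about it changes.
- The direction is not certain. Committee contact could also reveal problems absent from the record and raise the intervention count. This stands, and a symmetric rule deals with either direction.
- A condensed article may leave scoring detail to a manual. That is fair for detail in general. Here, though, the process that is described gives the assessor information in one arm only for a primary outcome, and the article claims protection that does not reach it.

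**Conclusion.** The concern holds as an open, one-sided path in how the DRP outcomes are ascertained. The article shows the ingredients: a discussion step in one arm, an unblinded assessor who took part in it, judgement-based DRP types, and no stated link between the 3-month score and a documented change. It does not show that DRPs were or will be dropped this way.

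The possible bias falls mainly on DRPs per patient. It is much smaller for the proportion with any DRP, on which the trial is sized: with two or three independent DRPs per affected resident, even the extreme case gives 45.4% or 48.6% instead of 50%. A reader might infer from the 20% row that re-scoring could easily explain the whole planned effect. That needs one in five affected residents to lose all their DRPs, which the article gives no reason to expect when residents have several. The medication-count outcomes are untouched.

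The true size is unknown. The figures rest on an acceptance rate from other studies, one proposal per DRP, independence between DRPs, and the plan's ICC. This is a cheap improvement worth making, not a flaw that invalidates the trial.

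**What to change.** State one scoring rule for both arms and both time points, based on the record and without using committee reasons:

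1. A baseline DRP counts as resolved only if the prescription, monitoring or clinical record documents the change. This includes a treatment target now reached or an adverse effect that has ended, so DRPs that resolve without a new prescription are not misclassified.
2. A DRP whose proposal was rejected, with the record unchanged, stays in the count.
3. New DRPs at 3 months are counted by the same criteria.
4. Intervention-arm DRPs that the committee set aside are reported separately.

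In the Discussion, replace the mitigation statement with one that says which parts of the DRP score are judgements and how the rule limits their effect.

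The cost is one scoring rule and one extra questionnaire field; where 3-month scoring is already complete, the rule would have to be applied by re-scoring from the record. The downside is that some clinically justified prescriptions stay counted as DRPs, equally in both arms, and the effect may look slightly smaller. The rule narrows the unblinded-assessor problem but does not remove it, so that limitation should stay in the article.

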### Usual care (control group)

In the control nursing homes, pharmacological treatments will be managed following standard procedures. Typically, primary care physicians only authorize and prescribe treatments proposed by nursing home physicians, with limited involvement in ongoing medication management. However, they have access to electronic clinical decision support tools aimed at improving prescribing quality. These include the self-audit tool which detects therapeutic duplications, polypharmacy, contraindications, and inappropriate treatment durations- and the PREFASEG (Safe pharmacological prescription) module, which alerts prescribers to potential interactions, contraindications, and redundancies when initiating new therapies.

### Measurement

Data were collected at baseline and at 3 months using the electronic prescription module of each patient’s electronic health record. The evaluation was conducted by the pharmacist implementing the intervention, who was not blinded to the study group allocation of nursing homes and patients (Table 1).➢ Outcome variables

**TABLE 1 T1:** Variables and measuring instruments.

Variable	Instrument	Application time	
		Basal	3 months
Sociodemographic variables	Questionnaire *ad hoc*	X	
Age			
Sex			
Length of time living in the nursing home			
Pharmacotherapeutic plan			
Description of the pharmacotherapeutic plan	ATC classification^a^	X	
Description and classification of the DPRs^b^ detected	Classification	X	
Clinical			
Comorbidity			
*Physical comorbidity*	Checklist	X	
*Psychiatric comorbidity*	Checklist		
*Global indicator*	*Charlson index*	X	
Complex Chronic Patient^c^	Checklist	X	
Advanced Chronic Care Model^c^	Checklist	X	
Functional capacity	Barthel index	X	
Cognitive status	SPMSQ^d^ Pfeiffer		
Clinical Results			
Drug related problems (DRP)^b^	Questionnaire *ad hoc*	X	X
*Number of DR P* ^b^ *per patient*			
*Proportion of patients with DRP*			
Polymedication	Questionnaire *ad hoc*	X	X
*Number of drugs a patient receives simultaneously*			
*Number of polymedicated patients*			
Results of the pharmaceutical review (only in the intervention group)			
Proposals for change	Questionnaire *ad hoc*	X	
Proposals implemented	Questionnaire *ad hoc*		X

^a^
ATC: anatomical therapeutic chemical classification system.

^b^
DRP: drug related problems.

^c^
According to the criteria of *Bases per a un model català d’atenció a les persones amb necessitats complexes. Conceptualització i introducció als elements operatius. Generalitat de Catalunya, 2017.*

^d^
SPMSQ: short portable mental status questionnaire.

Drug-Related Problems (DRPs) were quantified as total number, DRPs per patient, and the proportion of patients with at least one DRP. DRPs were classified into four categories: indication, appropriateness, effectiveness, and safety (Table 2).

**TABLE 2 T2:** List and classification of drug-related problems (DRP) considered in this study.

Category	DRP
Indication	- Medically unnecessary/not indicated/not appropriate for the health problem - Failure to prescribe a necessary medicine
Adequacy	- Medically inappropriate - Dose higher or lower than correct dosage - Incorrect administration frequency - Wrong drug form - Duration too long or too short
Effectiveness	- Failure to achieve the therapeutic goal - The goal is achieved but the intensity of the pharmacological treatment needs to be reduced - Not the most effective alternative based on evidence and/or clinical practice guidelines
Safety	- Allergy or adverse effect - Contraindication - Therapeutic duplication - Drug- drug interaction - Lack of analytical controls

This classification is based on the position statement of the Spanish Society of Primary Care Pharmacists (*Sociedad Española de Farmacéuticos de Atención Primaria*) (Socied ad Española de Farmacéuticos de Atención Primaria SEFAP, 2022).

Polymedication was measured as the number of medications taken concurrently by each patient and the number of polymedicated patients. Polypharmacy was defined as the chronic use of ≥10 medications (Duerden et al., 2013; Gnjidic et al., 2012). Topical treatments, eye drops, occasional treatments, and those used for acute conditions were excluded from this count. Fixed-dose combinations were counted according to the number of active ingredients. Multiple dosages of the same active ingredient were counted as one drug.➢ Secondary variables

Sociodemographic variables such as age and sex were collected. Regarding the pharmacotherapeutic plan, the number and classification of DRPs identified (by indication, appropriateness, effectiveness, or safety) were recorded.

Clinical variables included physical comorbidity, such as the presence of chronic conditions like diabetes, cardiovascular disease, respiratory disease, dementia, and cancer. Psychiatric comorbidity included diagnoses of depression, anxiety, psychotic disorders, and substance use disorders.

Comorbidity was also quantified using the Charlson Comorbidity Index (Charlson et al., 1987), which integrates age and 19 clinical conditions to provide a summary score correlated with 1-year and 10-year survival.

To assess chronic care complexity, we recorded the number of patients identified as Complex chronic patients (PCC) or as part of the Advanced chronic care model (MACA) (Departament de Salut, 2017). PCCs are defined by clinicians as having complex clinical management needs due to multimorbidity, a polypharmacy, clinical instability, resource use, and age extremes. MACA patients are those with a limited life expectancy and palliative care needs.

## Statistical methods

### Sample size

Based on prior observations and published studies, we assume that the proportion of patients with drug-related problems (DRPs) will be 50% in the control group (Vink et al., 2011; Costa et al., 2016; Garin et al., 2021). We expect to detect an absolute reduction of 10 percentage points in the prevalence of medication-related problems, from 50% in the control group to 40% in the intervention group. This difference is considered clinically meaningful, as even a modest reduction in such problems may lead to significant improvements in patient safety and care quality in the nursing home setting.

The sample size is calculated to account for the cluster design of the study, using the GRANMO calculator (https://www.datarus.eu/en/applications/granmo/). Assuming an alpha risk of 0.05 and a power of 0.80 in a two-sided test to detect a difference between proportions of 0.50 in the control group and 0.40 in the intervention group, a total of 24 clusters (12 per group) with 37 participants per cluster is required, including an estimated 10% loss to follow-up. A low intraclass correlation coefficient (ICC) of 0.001 is assumed. In the absence of published ICC estimates for this setting, we adopt a conservative value consistent with other studies involving individual-level binary outcomes with limited clustering. If the actual ICC or the number of participants per cluster differs substantially from expectations, we will conduct a sensitivity analysis to assess the potential impact on statistical power and precision.

Participants who die during the follow-up period will be considered lost to follow-up and excluded from outcome analyses. This expected attrition has been accounted for in the sample size calculation, which includes an estimated 10% loss due to mortality and other causes of dropout.

